## Abstract

**Background:**

The first years of life are a significant period for child development, when children are particularly sensitive and prone to crises. This early phase lays the foundation for healthy growth. Clinical assessment of psychological symptoms in early infancy and adequate treatment are both important in improving the diagnostic outcome and preventing later long-term developmental consequences. The most common psychological problems in the first 3 years of life are regulatory disorders. The aim of this trial is to investigate the efficacy of Parent-Infant Psychotherapy (PIP) for infants and young children (aged 0–36 months, diagnosed with at least one regulatory disorder) and their mothers, compared to care as usual (CAU).

**Methods:**

In this open multicentre randomised controlled trial, 160 mother-infant dyads are randomised to receive PIP or CAU for 6 weeks of intervention in clinical or outpatient (including home treatment) settings. The primary outcome is the maternal sensitivity (sensitivity scale of the Emotional Availability Scales (EAS)) after 6 weeks. Secondary outcomes include assessment of interaction, mental health problems, attachment, development, psychological factors, treatment adherence, health care system utilisation, and costs, after 6 weeks and 12 months.

**Discussion:**

This study will evaluate whether a manualised focus-based short-term psychodynamic psychotherapeutic intervention in mother-child dyads improves the care situation for families of children diagnosed with regulatory disorders, and helps prevent long-term psychopathologies. Assessment of the intervention in different settings will support the development of more tailored interventions for affected infants and their mothers.

**Trial registration:**

German Clinical Trial Register, ID: DRKS00017008. Registered 03/20/2019.

## Background

The most common psychopathologies in early childhood are regulatory disorders (e.g. excessive crying, sleeping and feeding disorders), which affect about 20% of all infants and toddlers [1]. Fortunately, the majority of these early mental health problems are transient. Yet there are major gaps in improving clinical outcome and development, in (1) adequate assessments of early psychopathological signs [2, 3] due to a lack of validated assessment methods, and (2) detection of severe clinical courses and subsequent treatment [1, 4]. The distribution of psychopathology seems to correspond with later developmental stages, but the description of symptoms in the early years of life do not fit within the framework of the common diagnostic classification systems of ICD-10 and DSM-V. Only in the last couple of years has the focus of research in this field shifted to diagnostic criteria for infants, with the development of the Diagnostic Classification of Mental Health and Developmental Disorders of Infancy and Early Childhood DC: 0–5™ [5].

A meta-analysis by Hemmi and colleagues [1] showed that parental mental health problems (e.g. depression, anxiety, obsessive-compulsive disorders) are potential risk factors for infant psychopathology. Moreover, Fraiberg, Adelson and Shapiro [6] underline the problem of transmission in parenthood in their concept of the ‘Ghosts in the nursery’. They explain the negative impact on parental functions using their own transgenerational experience when raising their children [6, 7]. The development of a strong, stable bond between mother and child is one of the most essential factors for an infant’s resilience and healthy development [8, 9]. Maternal sensitivity is well known to be a key factor in the mother-infant interaction and the development of a secure attachment to the mother [8–10].

Psychodynamic Parent-Infant Psychotherapy (PIP) within dyadic or triadic sessions aims to improve maternal sensitivity and attachment security [11]. Various studies have already demonstrated the efficacy of PIP in (1) reducing psychological symptoms (e.g. [12]), (2) improving maternal sensitivity (EAS), and (3) improving attachment security in high-risk samples [11, 13] compared with control groups and diverse interventions (e.g. education, support and medication) [11, 14, 15].

Nevertheless, the authors note some limitations such as overall low study quality and heterogeneous samples without clinical marker cut-offs. The meta-analysis by Hemmi et al. [1] also criticises the fact that most of the studies on regulatory disorders have focused only on singular regulatory disorders without recording data for any other coexisting mental health problems.

Thus, despite the clear benefits of attachment- and sensitivity-related interventions for the mother-child dyad [16], a corresponding study of PIP with validation in inpatient psychiatric departments is still needed. Moreover, recent developments in child psychiatry provide evidence for the efficacy of home treatment or home-based interventions by psychotherapists [17–19] . Home-based PIP interventions have been demonstrated to be effective in improving children’s attachment organisation [20], but other randomised controlled trials (RCTs) have reported no effects on attachment measures or maternal sensitivity [21, 22]. It should clearly be noted that there are wide methodological differences between these studies.

In summary, previous RCTs on the efficacy of PIP have dealt exclusively with specific risk groups and/or have taken place in outpatient – but not yet in inpatient – settings [12, 14, 22–24]. These studies, using validated assessment methods, found an improvement in attachment security and long-term effects in a child’s development, as well as symptom reduction [15]. An exploration and validation of PIP in inpatient psychiatry and non-inpatient treatment (e.g. psychiatric outpatient clinics, home treatment) is still pending [25].

The aim of this study is to assess the efficacy of PIP in young children (0–36 months, diagnosed with at least one regulatory disorder) and their mothers in clinical and outpatient settings compared to care as usual (CAU). CAU includes different approaches, from regular therapy sessions to psychiatric and paediatric health care.

## Methods and design

### Overview

The trial is part of the SKKIPPI research project, which is designed to evaluate integrated psychological-psychiatric care for parents and their children in the first 3 years of life. The overall project consists of a cohort study and two randomised controlled trials (RCTs) [26], performed under the auspices of the German Health Care Innovation Fund, which aims to improve the quality and integration of health care [27]. The cohort study investigates the occurrence of mental health disorders, psychosocial problems and health care use in the first 3 years of life, taking random samples from registry offices of three German regions [28]. Of the two RCTs, one focuses on mothers with postpartum mental disorders, and their children [29], while the present study focuses on children with regulatory disorders, and their mothers.

### Aims and hypotheses

This trial evaluates the efficacy of PIP in comparison to CAU regarding maternal sensitivity. The intervention will be assessed in inpatient (Psychosomatics / Parent-infant unit; PIU) or outpatient psychiatric departments via home visits by trained and certified PIP psychotherapists. It is expected that CAU will reduce symptoms of mental health problems in mother and child, but have little or no effect on maternal sensitivity. In comparison to CAU, PIP is particularly expected to enhance maternal sensitivity following the intervention and to increase the rate of securely attached children at 12 months follow-up. Additional analyses will address health care economics and the use of German health care services by mothers with children who have regulatory disorders, and the groups will be compared.

### Trial design

The two-armed, open, randomised, controlled multicentre study with parallel groups and blinded endpoint assessment (PROBE design; prospective randomised, blinded endpoint) with a six-week intervention is currently underway in Leipzig, Berlin, Potsdam and Hamburg. All study centres and participating clinics there provide focused and supervised certified PIP in accordance with a previously elaborated SKKIPPI Study Manual ([name], [name], [name]: SKKIPPI Study manual for Parent-Infant-Toddler Psychotherapy (PIP), Unpublished). Depending on the severity of the child’s pathological symptoms, and in agreement with parental preferences, a decision is made on treatment setting (in−/outpatient) before randomisation. Participants are then randomly assigned to either PIP or CAU, and data are collected at three measurement points: at baseline before intervention, immediately after treatment, and at 12 months follow-up. The biostatistician of the Institute for Social Medicine, Epidemiology, and Health Economics at the Charité – Universitätsmedizin Berlin generates the allocation sequence based on a computer generated random list, applying a 1:1 block randomisation with variable block length and stratified by setting (inpatient/outpatient) and study centre. Mother-child dyads are randomly assigned to either PIP or CAU.

Before being enrolled in the trial, participants are screened by a professional physician or psychotherapist for eligibility and clinical diagnoses. Only children receiving an ICD-10 diagnosis of regulatory disorder can take part in the study. Eligible mothers of these children are informed verbally about the study, and written informed consent must be given before randomisation. Afterwards, baseline assessments are carried out, and the 6 weeks of interventions start. At the end of treatment, participants are assessed again, as well as 12 months after baseline. Mothers will receive €100 as monetary compensation (25€ after Baseline, 25€ after 6 weeks follow-up and 50€ after the last assessment) until the 12-months follow-up. Throughout the study, the study nurse is in contact with the participants via phone calls or e-mails to schedule appointments. Treatment allocation is masked to the assigning personnel and there are no special criteria for discontinuing or modifying the allocated intervention (Fig. 1).

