### Outcomes

#### Primary outcome

The primary outcome will be maternal sensitivity measured after 6 weeks of intervention. Videotaped dyadic sessions of free-play interaction will be coded using the subscale ‘sensitivity’ of the emotional availability scales (EAS) [30]. EAS assesses the quality of the mother-child interactions using a seven-point Likert scale for maternal sensitivity. Independent and reliable coders blind to treatment allocation rate all the 15- to 20-min video scenes.

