### Data collection and monitoring

Researchers responsible for data collection are blind for randomisation and treatment group allocation. All data are stored under pseudonyms until the whole study is terminated. Data on the intervention will be unblinded after the last participant has completed the study. Only pseudonymous data sets will be analysed. There are formal rules for stopping the trial should a severe adverse event (SAE) occur. In the case of SAE the advisory board will be consulted. The consortium leader (LK) will report any SAE to the local ethics committees and all relevant parties. Standard operating procedures (SOPs) will be activated and will lead to exclusion of the participant and potentially to the termination of the trial. The participating scientists and study therapists are trained and qualified in all methods. All study therapists will receive training in PIP according to the SKKIPPI study manual. The SKKIPPI study manual is also the basis for the regular therapy adherence measurements.

The study centres are monitored based on the data collection status (mutual monitoring of the study centres by the study team) to ensure completeness and compliance with ethical considerations.

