#### Primary endpoint

The primary analysis of the primary endpoint (maternal sensitivity measured using the EAS subscale after 6 weeks) will be analysed using ANCOVA based on the FAS population using PIP versus CAU as the factor treatment group, EAS sensitivity at baseline as covariate, and the stratification variable treatment setting. Results will be displayed as adjusted means of the treatment group together with 95% confidence intervals and the respective *p* value (two-sided). The significance level is set at α =0.05. All further analysis is considered exploratory.

A secondary analysis of the primary endpoint will also be carried out using the ANCOVA model based on the PP population. Additional moderator analyses of the efficacy of PIP for a change in maternal sensitivity (EAS) will be conducted with treatment setting as the moderator, i.e. by additionally adding a ‘treatment group’ * ‘treatment setting’ interaction term to the model. Further moderator analyses regarding the efficacy of PIP will comprise maternal attachment type (AAI attachment) or maternal reflective functioning (AAI RF) as moderators.

In addition, models incorporating multiple imputation methods based on the PP population and a hierarchical regression model (including the therapist as a grouping factor and therapist’s adherence as covariate) will be used for sensitivity analyses of the primary outcome. To investigate the longitudinal change of the primary endpoint, linear mixed models (LMMs) incorporating both measurement points for each outcome (FAS population) will be computed. To explore further effects of additional predictors (such as the therapists carrying out the interventions), the models will be compared based on model fit values (AIC, the Akaike Information Criterion), with these predictors included in the model term.

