#### Missing data

After written informed consent and randomisation, participants can be excluded from the analyses only if there has not been any intervention, no data have been collected after randomisation, or at the participants’ express request after withdrawing from the study during the data collection phase. Primary statistical analyses of the primary and secondary endpoints are based on the FAS population without the imputation of missing data. For a sensitivity analysis, missing values for the primary endpoint will be imputed using Multiple Imputation methods for linear regression based on Markov chain Monte Carlo (MCMC) simulations. Imputation variables will be selected blinded for the intervention groups, and at least 5000 iterations and 100 imputations will be calculated.

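### As worded, the protocol puts randomisation before the baseline assessments in an open trial, so the baseline covariate of the primary ANCOVA may be measured after mothers know their arm

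*Protocol article*

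**What the plan says.** Trial design gives the sequence in two places. One paragraph has the treatment setting decided ahead of randomisation and continues: "Participants are then randomly assigned to either PIP or CAU, and data are collected at three measurement points: at baseline before intervention". The next paragraph says that "written informed consent must be given before randomisation. Afterwards, baseline assessments are carried out, and the 6 weeks of interventions start".

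The same section describes the trial as "The two-armed, open, randomised, controlled multicentre study with parallel groups and blinded endpoint assessment". Two further statements concern blinding. Under Primary outcome, "Independent and reliable coders blind to treatment allocation rate all the 15- to 20-min video scenes". Under Data collection and monitoring, "Researchers responsible for data collection are blind for randomisation and treatment group allocation". Mothers are nowhere described as blind, and the text does not say when they are told their arm.

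Under Primary endpoint, the primary ANCOVA has treatment group as factor, with "EAS sensitivity at baseline as covariate, and the stratification variable treatment setting".

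**The concern.** A baseline covariate is safe to adjust for because it cannot depend on the assigned arm. That holds by design when it is measured before allocation. It also holds when the random number has been drawn but nobody who can influence the measurement knows the result. It is no longer guaranteed once the mother knows.

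Here the covariate is the mother's own behaviour in filmed free play. A mother who knows that she will receive PIP, or that she will not, may play differently or answer questionnaires differently. A blinded coder would score that changed behaviour correctly, and the change would enter the model as if it were a pre-existing difference between the arms.

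The main stake is the adjusted difference in EAS sensitivity at 6 weeks, the trial's one confirmatory result. Baseline self-reports such as the EPDS, which is taken at every measurement point, are open to the same influence, but the analyses that use them are declared exploratory.

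**Working it through.** **Step 1: the order in the text.**

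| Event | Where the text places it (Trial design) |
|---|---|
| Choice of in- or outpatient setting | before randomisation |
| Written consent | before randomisation |
| Baseline assessments | before the intervention; named after random assignment in one paragraph and after the consent-and-randomisation clause in the next |
| Disclosure of the arm to the mother | not stated |

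Two events are tied explicitly to randomisation. Baseline is tied only to the intervention. Both paragraphs name randomisation first, and no other section reverses that.

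**Step 2: what blinding covers.** Blinded coders and data collectors protect against a rater or interviewer favouring one arm. They do not act on the mother's behaviour or answers.

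**Step 3: the effect on the ANCOVA.** The plan gives no figure on this point to reproduce. The ANCOVA estimate is

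adjusted difference = (difference in 6-week means) − b × (difference in baseline means),

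with differences taken as PIP minus CAU and b the within-group slope of 6-week EAS on baseline EAS. Under randomisation and with complete outcomes, the first term has the total effect of assignment as its expected value. If baseline precedes knowledge of the arm, the baseline difference has expected value 0. If knowing the arm shifts baseline by s (PIP minus CAU), it has expected value s, so

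bias = −b × s.

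Inputs:
- d = 0.64, from Sample size considerations, used only as a yardstick.
- s = 0.1 to 0.2 SD in either direction: an assumption. The protocol gives no estimate.
- b = 0.3 to 0.7: an assumption. In SD units, with equal SDs at the two times, this is the within-group correlation.

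| b | Size of s (SD) | Size of bias = b × s (SD) | Bias / 0.64 |
|---|---|---|---|
| 0.3 | 0.1 | 0.03 | 4.7% |
| 0.3 | 0.2 | 0.06 | 9.4% |
| 0.5 | 0.1 | 0.05 | 7.8% |
| 0.5 | 0.2 | 0.10 | 15.6% |
| 0.7 | 0.1 | 0.07 | 10.9% |
| 0.7 | 0.2 | 0.14 | 21.9% |

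The sign is opposite to the shift. If PIP mothers look more sensitive than CAU mothers at baseline because they know their arm, the benefit of PIP is understated. If they look less sensitive, it is overstated.

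**Step 4: after re-ordering.** With baseline complete before disclosure, s = 0 by design and the bias term vanishes for any b. Neither the sample size nor the power changes.

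**The case against.** The strongest reply is that the text is loose and the conduct may be sound. In the consent sentence, randomisation only qualifies when consent is due, so the following word could mean after consent. The other sentence joins assignment and data collection with a simple conjunction and may just be listing the measurement points. Fig. 1 (participant flow) and Fig. 3 (schedule) would normally settle the order, and neither is shown. An open trial need not disclose the arm before baseline, and blinded data collectors make disclosure at the baseline visit less likely. All of this stands, and it is why the point is conditional. It does not remove the point: randomisation first is the natural reading, and nothing available contradicts it.

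Three stronger readings are tempting and are not supported:

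- *Mothers do know their arm at baseline.* The protocol does not say so. The bias arises only if they do.
- *Dyads who leave on learning their arm are lost to the primary analysis because of this order.* Such dyads would usually lack the 6-week EAS as well. The primary ANCOVA does not impute, so it would drop them whether or not they had a baseline video, and re-ordering would not bring them back. The exclusion rule under Missing data, "no data have been collected after randomisation", fits either sequence and is no evidence of order.
- *The primary result is biased by 5% to 22%.* Those percentages are products of assumed inputs. Nothing in the protocol supports a particular shift in blind-coded sensitivity.

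**Conclusion.** The point holds conditionally. As worded, Trial design puts randomisation before baseline, and no text available places baseline before randomisation or disclosure. If mothers learn their arm before the baseline video, the primary ANCOVA adjusts for a covariate that assignment can affect, and the blinding described does not fully prevent this. Under the stated assumptions the bias would be 0.03 to 0.14 SD, opposite in sign to the baseline shift. The true size is unknown, and it is zero if disclosure follows baseline.

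The section needs changing in either case. If practice is sound, the published order is misleading. If practice follows the text, the primary covariate is exposed. Because the correction is cheap and removes the problem by design, it should be made, but the documents do not show that the trial's result is compromised.

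**What to change.** **Sequence.** Reword Trial design, and conduct the trial accordingly, as: consent; baseline assessments including the EAS video and self-reports; randomisation and disclosure; start of treatment. At the least, baseline must be complete before the arm is disclosed. The protocol version is dated January 2021 and recruitment was expected to run to April 2022, so this could still apply to the dyads remaining at that date.

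**Dyads already enrolled.** Report the actual order of baseline, randomisation and disclosure where dates exist, and the number lost between randomisation and baseline in each arm. Add a sensitivity analysis of 6-week EAS sensitivity by treatment group and setting, without the baseline covariate, in all dyads with a 6-week outcome. This is free of the mechanism above and keeps any dyad that has an outcome but no baseline.

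**Cost.** Re-ordering means a short delay before the arm is disclosed and some baseline assessments on dyads then not randomised. The sensitivity analysis is less precise: omitting the covariate multiplies the standard error by about 1/√(1 − r²), which is 1/√0.91 = 1.05 for a correlation of 0.3 and 1/√0.51 = 1.40 for 0.7. It should therefore support the primary ANCOVA and not replace it. Disclosure dates may not have been recorded for early dyads; if so, that should be stated.

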**Fig. 1 Fig1:**
[figure not shown]
Standards of reporting trials (CONSORT). Diagram showing the planned flow of participants through the study

### Participants and eligibility screening

We include infants and young children aged 36 months or younger (Table 1). Participation is conditional upon written informed consent from the legal guardians. All participants are carefully informed about the study goals and assessment.

**Table 1 Tab1:** Inclusion and exclusion criteria

Inclusion criteria	
• Infants aged 36 months or younger	
• Infants diagnosed (by a certified paediatrician, psychiatrist or psychotherapist) with at least one regulatory disorder	
• Mothers must speak German to a sufficient level and understand the aims of the study	
• Mothers must be in a psychological state that allows them to participate in the study	
Exclusion criteria	
• Mother or child is already participating in other clinical trials	
• Mother or child is receiving any other form of psychotherapy	
• Mother is dealing with acute substance abuse, or has suicidal tendencies or acute psychosis	
• Child has a suspected alcohol embryopathy, or severe organic impairments	

